#### Efficacy analysis

Pain intensity will be analyzed at individual time points and by AUC. The mean AUCs at 0–24 h and 0–48 h for Naldebain^®^ and PCA will be calculated using the trapezoidal method. These values will then be compared using a two-sample *t* test.

For total postsurgical consumption of supplemental analgesics, opioid and NSAIDs will be counted separately. A two-sample *t* test will be used to compare treatment groups. Between-group differences at baseline in answers to BPI questions based on rating scales will be analyzed using a two-sample *t* test; an analysis of covariance model will then be used for postsurgical BPI assessments with baseline response as the covariate. A chi-square test will be used to compare the Naldebain^®^ and PCA groups with respect to patient satisfaction with postsurgical analgesia. Length of postoperative hospital stay will be tested using a two-sample *t* test.

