**Methods/design:**

A total of 110 patients will be recruited and randomized into two treatment groups. Group 1 receives a single dose of Naldebain^®^ intramuscularly 24 ± 12 h prior to surgery. Group 2 receives intravenous patient-controlled analgesia (PCA) with fentanyl through 48 h postsurgery. Both groups will have follow-up observations until the final visit (day of discharge, day 6–30). The primary efficacy endpoint is to assess time-specific pain intensity calculated as the area under the curve (AUC) of a visual analog scale at individual time points and by using total AUC. Safety endpoints—including incidence of treatment, emergent adverse events, and percentage of abnormality from baseline to final visit—in vital signs, laboratory tests, and injection site evaluations will also be analyzed. Statistical analyses will be performed on the data to compare the two groups.

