## Methods and design

### Overall design

A randomized, positive-controlled, single-dose, parallel-design study will be conducted with 110 male and female patients scheduled to undergo elective laparotomy to assess the safety and efficacy of an intramuscular injection of Naldebain^®^. The study was designed to include a 5% dropout rate as taken from a previous published work [8].

A total of 110 eligible hospitalized patients will be randomized into one of two treatment groups in a 1:1 ratio. Group 1 is the intramuscular Naldebain^®^ (IM-Naldebain^®^ group) and Group 2 is the intravenous PCA with fentanyl (IV-PCA group). Group 1 receives a single dose of Naldebain^®^ (150 mg nalbuphine sebacate) intramuscularly 24 ± 12 h before surgery. Group 2 receives intravenous PCA with fentanyl through 48 h postsurgery. If PCA with fentanyl is deemed unnecessary by both investigator and patient, the PCA machine can be removed prior to the completion of 48 h as required. If patients require additional medication for treatment of pain, ketorolac and morphine can be used as supplemental analgesics as required. Both groups will undergo follow-up observation until the final visit (from the day of discharge through day 6–30). Statistical analyses will be performed on the data to compare the two groups.

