### Number of patients and randomization

Assuming an equivalence margin of 10 and a standard deviation of 18 [8], 104 patients are required to achieve 80% power using the non-inferiority test with a one-sided 97.5% confidence interval (equivalent to a two-sided 95% confidence interval). A total of 110 eligible patients will be randomized in this study, with a predicted dropout rate of 5%. The participants will be randomized using sealed, opaque, individually numbered envelopes, with a restriction of selecting one per person. The envelopes contain data sheets with information on group allocation and the randomization number, generated by the statistician with SAS software. A randomization schedule stratified by center has been prepared. The schedule links sequential numbers to treatment codes allocated randomly. The schedule was prepared with a 1:1 block randomization ratio.

Eligible patients will be randomized to the study medication in accordance with the randomization schedule. The next eligible patient will receive the study medication with the lowest available randomization number. Patients will be only given the study medication carrying their randomization number.

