#### Hypotheses and level of significance

Statistical analyses will be performed on the data to compare the Naldebain^®^ group with the PCA group. All statistical tests will be two-sided and evaluated at a level of significance of 0.05.

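### The article sizes the trial for non-inferiority, but its hypothesis and efficacy sections prescribe a two-sided difference t test and never bring in the margin

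*Protocol article*

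**What the plan says.** The title calls this a non-inferior trial, and the abstract's Discussion says the study will show whether Naldebain is no less efficacious than fentanyl PCA. Number of patients and randomization builds the sample size on that basis: "Assuming an equivalence margin of 10 and a standard deviation of 18", "104 patients are required to achieve 80% power", "using the non-inferiority test with a one-sided 97.5% confidence interval (equivalent to a two-sided 95% confidence interval".

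The two sections that fix the analysis read differently.

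- Hypotheses and level of significance states no non-inferiority hypothesis. Its rule is: "All statistical tests will be two-sided and evaluated at a level of significance of 0.05".
- Efficacy analysis computes mean AUCs over 0–24 h and 0–48 h and continues: "These values will then be compared using a two-sample" t test. It gives no margin, confidence interval or criterion for success. Supplemental analgesic use and length of stay get the same kind of test.

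The primary variable is also described unevenly. Objectives and Study endpoints both name the AUC of VAS scores through 48 h. The abstract describes the primary endpoint as assessed "at individual time points and by using total AUC". Efficacy analysis lists individual time points and the two AUCs without saying which one carries the conclusion.

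**The concern.** A two-sample t test at two-sided 0.05 tests whether the mean difference is zero. A non-inferiority trial must reject a different hypothesis, namely that the new treatment is worse by at least the margin. The margin of 10 appears only in the sample-size paragraph, so the primary comparison as written tests a hypothesis other than the one the trial was sized for.

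The headline conclusion is at stake. A non-significant difference does not show non-inferiority, and noisier data make non-significance easier to reach. Without a stated rule, the report would have either no formal verdict or room to take p > 0.05 as one.

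**Working it through.** **Inputs.** Margin 10, SD 18, 80% power, one-sided 97.5% interval (alpha 0.025), 104 patients before dropout, 5% dropout and 110 in total come from Number of patients and randomization. The 1:1 allocation is from Overall design. Two assumptions are mine. The true difference used for sizing is 0, which is not stated but reproduces the stated number. The 10 and the 18 are both taken to be on the scale of the analysed AUC.

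**Step 1: reproduce the sample size.**

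- Normal approximation: n per arm = 2 × (1.960 + 0.842)² × 18² / 10² = 50.9, so 51 per arm and 102 in total.
- With the noncentral t distribution, 51 per arm gives 79.3% power and 52 gives 80.1%, so 52 per arm and 104 in total. This matches.
- Dropout: 104 / 0.95 = 109.5, so 110. This matches.
- Alternatives that do not match: an equivalence design with two one-sided tests needs 138 (one-sided 0.025) or 112 (one-sided 0.05), and a one-sided 0.05 non-inferiority test needs 82.

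The stated number therefore fits the non-inferiority test that the paragraph names. It does not fit an equivalence test, despite the term used for the margin.

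**Step 2: precision.** Standard error = 18 × √(2/52) = 3.53. The 95% half-width is about 7.0. A margin rule would succeed when the observed difference (Naldebain minus PCA) is below about 10 − 7.0 = 3.0.

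**Step 3: what the prescribed test delivers, at 52 per arm and SD 18.**

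| True difference (Naldebain minus PCA) | t test non-significant | Upper 95% limit below 10 | Non-significant but upper limit 10 or more |
|---|---|---|---|
| 0 | 95% | 80% | 17% |
| 5 | 71% | 29% | 42% |
| 10 (the margin) | 19.9% | 2.5% | 17% |

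The 19.9% is 1 − 0.801. A true difference of 10 lies as far from 0 as a true difference of 0 lies from the margin, so the two-sided test has 80.1% power there.

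**Step 4: which t-test results settle the question.** Significant superiority puts the upper limit below 0, and so below 10. Its probability is about 2.5% when the true difference is 0. A non-significant result leaves non-inferiority open. A result significantly worse than PCA yet non-inferior would need an interval lying wholly between 0 and 10. The expected full width is 2 × 7.0 = 14, and no such result occurred in 400,000 simulated trials at any of the true differences tabulated.

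**Step 5: unit of the margin.** The margin is given as 10 with no unit, while the VAS runs from 0 to 10 cm. Read as a single VAS score, 10 is the whole scale. Read as cm·h over 48 h, it is 10/48 = 0.21 cm on average. An interval cannot be compared with the margin until the scale is stated.

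**The case against.** The strongest reply is that the sample-size paragraph already fixes the margin, the type of test and the interval. It equates the one-sided 97.5% interval with a two-sided 95% one, so the two-sided 0.05 level does not conflict on alpha. A two-sample t framework also produces exactly the interval to set against 10. The article is condensed, and an operational decision rule is often left to the analysis plan.

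Much of this stands. A reader might infer that the trial cannot answer its non-inferiority question. The documents do not support that: only the p-value as written fails to answer it, and the planned data and sample size can. A reader might also take 20% as the plan's type I error. It is not, because nothing in the article tells anyone to read p > 0.05 as non-inferiority. The figure shows the cost of that misreading.

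A third inference would be that the plan allows a claim on any of several endpoints. Objectives and Study endpoints each name one primary variable, the AUC through 48 h, and no rule permits success on another. The loose wording in the abstract and in Efficacy analysis needs aligning, but it does not support an inflated error rate.

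The reply fails on the main point. The article is not silent about the primary analysis: it has a hypotheses section and an efficacy section, and both specify a test of no difference. That is a mismatch with the sizing paragraph, and not just detail left to another document.

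**Conclusion.** The point holds as a mismatch between the design and the stated analysis, and it must be corrected because the trial's main conclusion depends on it. As written, the primary p-value tests a zero difference and gives no non-inferiority verdict unless Naldebain is significantly superior. If non-significance were taken as not less efficacious, the false-claim rate at a true deficit equal to the margin would be about 20%, against 2.5% under the margin rule. These figures assume 52 evaluable patients per arm, SD 18, and a margin and SD that both refer to the analysed AUC. The uneven naming of the primary variable is a secondary matter of wording.

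**What to change.** Revise Hypotheses and level of significance and Efficacy analysis for the primary endpoint, before the primary comparison is run:

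- State H0: mean AUC 0–48 h difference (Naldebain minus PCA) ≥ margin, against H1: difference < margin. Higher AUC means more pain.
- Conclude non-inferiority only if the upper limit of the two-sided 95% confidence interval for that difference is below the margin. Report it in both the ITT and PP populations already planned under Analysis populations.
- State the unit and scale of the margin and SD so that they match the analysed AUC, and call it a non-inferiority margin throughout.
- Name AUC 0–48 h as the only variable carrying the claim, with AUC 0–24 h and individual time points supportive. Align the abstract with Objectives and Study endpoints.

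The cost is wording only, with no new data. The sample size stays at 104 (110 with dropout), provided the margin and SD prove to be on the AUC scale. At 52 per arm the rule has 80% power at a true difference of 0 and a 2.5% false-claim rate at the margin, in a single analysis population. If success is to be required in both populations, the plan should say so; the power cost of that has not been worked out here.

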### Study assessments and procedures (see Table 1)

#### Schedule of assessments

##### Screening (days −30 to −1; all study patients)

The nature of the study, as well as the potential risks and benefits associated with study participation, are fully explained to all potential patients. The following are obtained: 1) informed consent; 2) demographic information, including sex, age, BMI, and type of surgery; 3) vital signs, including temperature, respiratory rate, blood pressure, and heart rate; 4) medical history, including medication use and any history of allergies; 5) physical examination; 6) laboratory testing, including hematological and biochemical tests, and urinalysis; 7) electrocardiogram (ECG) and x-ray; and 8) BPI is evaluated at day –1.

**Table 1 Tab1:** Study event flowchart

Period	Screening	Study period						
Study day	−30 to −1	−1	0	1	2	3–5	6	Discharge
Informed consent	X							
Medical history	X							
Demographic data	X							
Physical examination	X							X
Vital signs	X	X	X	X	X	X	X	X^d^
Injection site evaluation		X^b^	X^b^	X^b^	X^b^	X^b^	X^b^	X^b,d^
Laboratory tests	X	X^a^						X
12-lead ECG/chest x-ray	X							
Inclusion/exclusion criteria		X						
Randomization		X						
Naldebain^®^ administration		X^b^						
Surgery			X					
Pain assessment		X	X	X	X	X	X	
BPI		X			X		X	
Patient satisfaction								X
Concomitant medication	X	X	X	X	X	X	X	X^d^
Adverse event record		X	X	X	X	X	X	X^d^
Drug accountability for fentanyl			X^e^	X^e^	X^e^			
Discharge								X^c^
End of study								X

*BPI* brief pain inventory, *ECG* electrocardiogram

^a^Additional laboratory tests are requested as required by the investigator

^b^Only for subjects who are randomized to the Naldebain^®^ group

^c^Patients can discharge on day 6–30; patients still hospitalized after day 6 do not serve as a protocol deviation/violation or serious adverse event

^d^For patients who are discharged on day 6, the assessment is performed only once

^e^Only for subjects who are randomized to the patient-controlled analgesia (PCA) group

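### The five-level ordered satisfaction rating is compared by a chi-square test that ignores the order, which costs about 17 to 24 points of power for a consistent shift

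*Protocol article*

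**What the plan says.** Table 2 and the Final visit section define satisfaction as one question with five graded answers, coded 1 (best) to 5 (worst). Study endpoints lists it as a secondary efficacy endpoint. Under Efficacy analysis, "A chi-square test will be used to compare the" Naldebain and "PCA groups with respect to patient satisfaction with postsurgical analgesia". No trend test, rank test or grouping of levels is named there. Fisher's exact test appears as an alternative only under Safety analysis. The general rule is "All statistical tests will be two-sided and evaluated at a level of significance of 0.05".

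For the neighbouring endpoint, "Length of postoperative hospital stay will be tested using a two-sample" *t* test. Footnote c of Table 1 states "Patients can discharge on day 6–30", and the Final visit section repeats that window.

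The protocol gives no expected satisfaction shares, no mean or standard deviation of stay, and no power for any secondary endpoint.

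**The concern.** A chi-square test on a 2×5 table asks whether the two sets of shares differ in any way at all. It gives the same answer if the columns are shuffled. The question a reader will have is narrower: are patients in one arm more satisfied than in the other? For that question the test spreads its sensitivity over 4 degrees of freedom when one would do, and its p-value carries no direction or effect size. A real and consistent difference in satisfaction could be missed in a trial of 110 patients.

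Length of stay raises a milder issue. Recorded stay cannot fall below day 6 under the window, so part of any true shortening cannot appear in the data, whichever test is used.

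**Working it through.** **The plan's own figure.** The only sample size stated is for the primary endpoint: "Assuming an equivalence margin of 10 and a standard deviation of 18", and "104 patients are required to achieve 80% power using the non-inferiority test with a one-sided 97.5% confidence interval". With a true difference of 0 (not stated, assumed), n per arm = 2 × (1.960 + 0.842)² × 18² / 10² = 50.9, so 51 per arm, 102 in all. The *t*-based calculation gives 52 per arm, 104 in all, with 80.1% power. Then 104 / 0.95 = 109.5, so 110. The figure reproduces and this point does not affect it. With 1:1 allocation there are 55 per arm.

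**Analytic guide.** For 80% power at two-sided 0.05, the required noncentrality is 7.85 with 1 degree of freedom and 11.94 with 4. The ratio is 11.94 / 7.85 = 1.52. If the whole effect lies along the ordering, the unordered test needs about one and a half times the information.

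**Simulation of satisfaction.** Let C be the cumulative share at or better than a given level in the PCA arm. The Naldebain arm is given cumulative odds OR × C / (1 − C). Example: for PCA shares 30/45/15/7/3% and OR 2.5, the top level has odds 0.30 / 0.70 × 2.5 = 1.071, a share of 51.7%. Each scenario used 4,000 trials, 55 per arm, two-sided 0.05. Shares and odds ratios are assumptions.

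| Assumed PCA shares (%) | OR | Chi-square | Wilcoxon | Gap (points) |
|---|---|---|---|---|
| 30/45/15/7/3 | 2 | 29% | 49% | 20 |
| | 2.5 | 48% | 73% | 24 |
| | 3 | 66% | 86% | 20 |
| 45/40/10/4/1 | 2 | 27% | 47% | 19 |
| | 2.5 | 46% | 67% | 21 |
| | 3 | 62% | 81% | 19 |
| 20/20/20/20/20 | 2 | 32% | 52% | 21 |
| | 2.5 | 54% | 76% | 22 |
| | 3 | 72% | 89% | 17 |

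Gaps are taken before rounding. A fourth set of shares, 30/40/15/10/5%, gives 49% against 73% at OR 2.5.

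**Is sparsity the cause?** With equal arms, an expected count below 5 requires fewer than 10 of 110 patients in a category, a pooled share under about 9%. At least one such cell occurred in over 99% of simulated trials with the two skewed sets of shares in the table, but in under 8% with flat shares. The power gap is about the same in both, so sparsity does not drive it. With no true difference, the chi-square rejected in 3% to 5% of trials, so type I error is held.

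**Length of stay.** Take lognormal stays with log-SD 0.35 and medians of 6, 7 and 8 days (assumptions), shorten every stay by 1 day, and replace values below 6 by 6. The difference in means is then 0.41, 0.59 and 0.72 day. With whole days limited to 6–30 and 55 per arm, power is 28–30% for the *t* test and 37–40% for the Wilcoxon test. Under a proportional shortening instead (medians 7, 8 and 10; log-SD 0.3 or 0.5), the *t* test is within about 0 to 6 points of the Wilcoxon test. The floor itself costs the *t* test about 1 to 11 points and the Wilcoxon test about 0.5 to 8.

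**The case against.** The strongest objection is that a proportional-odds shift is the alternative that most favours a rank test. One fixed injection against patient-controlled dosing might polarise opinion instead. With PCA shares 30/40/15/10/5% and Naldebain shares 45/20/10/15/10% (assumed), the chi-square has 57% power and the Wilcoxon test only 7–8%. This stands as a real downside, and it is why the shares by arm should be reported with the test. It does not make the chi-square the better default for a scale built to run from best to worst.

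A second objection is that the protocol does not say Pearson, 4 degrees of freedom or ungrouped levels, and that a separate analysis plan may specify a trend version or a small-cell rule. That is fair as to detail, and the finding is therefore conditional on the nominal reading. The choice of a chi-square test is nevertheless one the document makes, not one it leaves open.

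Two stronger readings are tempting. A reader might infer that sparse cells make the satisfaction test unreliable. The protocol gives no shares from which to predict sparsity, and the simulations show neither an inflated error rate nor a dependence of the power loss on it. A reader might also infer that the *t* test on stay loses much of its power. Under the models above its deficit against a rank test is about 0 to 6 points, or roughly 10 points where both tests are weak. A large deficit appears only if 5–10% of patients are additionally assumed to stay 15–30 days (for example 26% against 77% at median 7 with 5%), and it is there with or without the floor. The documents give no distribution to support that. A difference in mean days is also a legitimate target in a trial whose Background and Discussion refer to cost of care.

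**Conclusion.** The point holds for satisfaction. Read as a nominal 2×5 test, the planned chi-square gives up about 17 to 24 percentage points of power against an order-using test for a consistent shift, at 55 per arm and assumed odds ratios of 2 to 3. The gap changes little across the category distributions tried. It is a loss of efficiency and interpretability on a secondary endpoint for which no power is claimed, not a fault of validity.

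For length of stay only a caution on interpretation holds. The day 6–30 window attenuates a true 1-day shortening to about 0.4–0.7 day under the assumed lognormal stays with medians of 6 to 8 days. No choice of test recovers what the floor removes. The claim that both secondary comparisons lose much of their power through the choice of test is not supported.

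**What to change.** In Efficacy analysis, replace the chi-square test for satisfaction with a Wilcoxon rank-sum test or a proportional-odds model. Report the common odds ratio with its 95% confidence interval and tabulate the five category shares by arm. The test may be stratified by centre, as the randomization is; this is optional.

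The cost is a change of wording, with no extra patients or data. The price is low sensitivity to polarised, non-monotone differences, which the tabulated shares would reveal.

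For length of stay, add a sentence saying that the discharge window bounds recorded stay at day 6 and that a null result is not evidence of no effect. A rank test with medians may be added as a precaution; it does not correct a demonstrated large loss.

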#### Interim analysis

No interim analysis will be performed.

### Ethical and regulatory aspects

#### Good clinical practice

This study will be conducted in compliance with the following documents: 1) the International Conference on Harmonization (ICH) Harmonized Tripartite Guidelines for Good Clinical Practice (GCP) 1996; 2) the Taiwan Good Clinical Practice, January 6, 2005; and 3) the Declaration of Helsinki.

#### Institutional review board approval

The study is being conducted under the supervision of an IRB/IEC. ICH guidelines require studies to have obtained approval from an IRB (KMUHIRB-F(I)-20,170,089) prior to the enrollment of human subjects into a study.

#### Delegation of investigator responsibilities

All investigators are responsible for the conduct of the trial in accordance with the protocol. In addition, the responsibilities of an investigator extend to the following: 1) providing sponsors with written documentation that the study protocol, any protocol amendments, and informed consent forms have received IRB/IEC approval; 2) reporting to the IRB/EC as required (the IRB/EC must assume continued responsibility for the study and review the research on an annual basis); 3) maintaining a file of all communications with the IRB/EC on issues related to the clinical trial; and 4) conducting the study according to the protocol, ICH–GCP guidelines, and in accordance with the Declaration of Helsinki.

